## 16.3 statistical analysis

This section is an overview of the statistical analysis. It provides general provisions on how to collect data and display data in clinical studies. The final version of the statistical analysis plan (SAP) will be completed before the database is locked. SAP will specify all "pre-defined, planned analyzes".

### 16.3.1 Statistical analysis of data sets

**Full Analysis Set (FAS):** The full analysis set is the main efficacy evaluation population of this study, and all valid variables will be analyzed by FAS. According to the basic principle of intention-to-treat (ITT) analysis, all subjects randomized into groups and those with more than one medication record and efficacy evaluation will be included in the full analysis set. When choosing FAS to analyze, the estimate of the missing value, the last observation carried forward (LOCF) estimation method can be used.

**Per Protocol Set (PPS):** Includes all subjects who complete the protocol or have no serious breaches of the trial. The exact definition of a serious violation of the program will be finalized at the time of data review and may generally include the following situations (but not limited to these cases): failing to meet the main inclusion criteria, serious disturbance of drug efficacy after treatment, poor compliance, exceeding the time window of following-up and so on. PPS is the secondary analysis of the effectiveness of the crowd, but if the results are inconsistent with the whole analysis set, detailed analysis of the

inconsistent results are needed.

**Safety Data Set (SS):** A safety data set is defined as a subject that receives drug treatment at least once. In the entire safety analysis, patients with incorrect treatment (for example, randomized to the standard antiplatelet combining delayed intensive statin therapy groups were given enhanced antiplatelet therapy) would be assigned to the actual treatment group.

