| Statistical analysis | 
Statistical analysis will be conducted with SAS 9.4. The two-sided <math>P < 0.05</math> is considered statistically significant.
 
1. Major null hypothesis:
 
1) In patients with acute mild ischemic stroke or high-risk TIA patients attributed to extracranial or intracranial atherosclerosis treated within 72 hours of ictus, there is no difference in the risk of a new stroke within 90 days between subjects with intensive antiplatelet therapy and those with standard antiplatelet therapy.
 
2) In patients with acute mild ischemic stroke or high-risk TIA patients attributed to extracranial or intracranial atherosclerosis treated within 72 hours of ictus, there is no difference in the risk of a new stroke within 90 days between subjects with immediate intensive statin therapy (atorvastatin 80mg/d) and delayed intensive statin therapy (atorvastatin 40mg/d).
 
3) In patients with acute mild ischemic stroke or high-risk TIA patients attributed to extracranial or intracranial atherosclerosis treated within 72 hours of ictus, there is no difference in the risk of a new stroke within 90 days between subjects with intensive antiplatelet combined with immediate intensive statin therapy (atorvastatin 80mg/d) and standard antiplatelet combined with delayed intensive statin therapy (atorvastatin 40mg/d).
 
2. Data sets of statistical analysis : intention-to-treat (ITT) population
 
3. Statistical analysis methods:
 
3.1 The balance analysis of basic values (comparison between groups of baseline characteristics)
 
1) The measurement data will be tested by t test or Wilcoxon rank sum test;
 
2) The enumeration data between groups are compared with chi-square test, Fisher's exact probability method or Wilcoxon rank sum test.
 
3.2 Efficacy analysis
 
1) Primary outcome:
 
 
Kaplan-Meier analyses will be used to evaluate survival curves for the primary endpoint, and survival curves will be compared by another factor stratification of the analytic design and using the Cox regression model Wald test. First, marginal effects will be compared between intensive and standard antiplatelet therapy, and also between immediate intensive statin therapy (atorvastatin 80mg/d) and delayed intensive statin therapy (atorvastatin 40mg/d). These are independent comparisons, they have no effect on the type I error rate. For comparisons of two therapies, the primary outcome of stroke will be considered statistically significant if the p-value is <math>< 0.05</math>. Second, if either intensive antiplatelet or immediate intensive statin therapy (atorvastatin 80mg/d) is statistically significant, the effects between combined intensive antiplatelet and immediate intensive
 
 |

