#### **7.5.2 Discontinuation from the study drug permanently**

- 1) Patient's decision. Patients can discontinue the study anytime they want unless it will affect their treatment.
- 2) Investigator's decision. Including but not limited to the following circumstances:
  - h) Primary outcomes (ischemic or hemorrhage stroke) occur
  - i) Pregnancy or preparation for pregnancy
  - j) Incorrect enrollment that does not meet the inclusion/exclusion criteria puts the patient at higher risk
  - k) Serious noncompliance
  - l) Emergence of adverse events that investigators believe may put patients at higher risk of continuing treatment
  - m) Definite indications for anticoagulant agent
  - n) Investigators decide it is inappropriate to restart the study drug after discontinuation

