#### **7.6 Quit from study**

Those who quit the study should not be included again. The randomization number and study drugs of this subject should not be used again. Randomized patients must not be replaced. Investigators should confirm the withdrawal along with the monitoring committee. Subjects who were randomized and had one or more doses recorded were required to complete the calendar visits according to the protocol.

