### 10.2 Day of Randomization

- Record basic demographic information, medical and medication history and physical examination of subjects
- Conduct ABCD score (for TIA patients), EQ-5D score and neurological examination (including mRS and NIHSS).
- Apply 12-lead electrocardiogram (ECG) to rule out atrial fibrillation, sick sinus syndrome and second or third degree atrioventricular block.
- Subjects obtain random code, and receive a drug box (for phase 1) in accordance to the

randomization number to supply the study drug used from day 1 to day 21. Study drugs should be taken as soon as the randomization is finished (within 1 hour after randomization). Instructions for taking the first study drug should be given by the investigator. (The first dose includes the total dose of medication taken by the patient after the onset of illness, taken in the ambulance and emergency room, and taken after admission to the hospital).

- Fasting laboratory tests should be completed within 24 hours after randomization (Including routine blood counts, biochemical panel [hepatic function, kidney function, blood lipid, creatine kinase], glycated hemoglobin, homocysteine, coagulation function). Fasting venous blood sample should be collected at the same time, and serum, plasma and white blood cells should be extracted and stored separately (Instructions are listed in the biological sample collection handbook). If not, 72 hours after randomization is the final deadline.
- Complete the initial diagnosis of the initial event for subjects.
- High-resolution MRI of intracranial arteries (high-resolution MRI subgroup only): need to be done within 24 hours of randomization completion.

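### The main efficacy set in section 16.3.1 appears to require more than one medication record, which conflicts with the Summary's ITT population and can exclude observed early strokes

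*Supplement*

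**What the plan says.** The latest protocol version (4.0) describes the efficacy population in two places.

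- Summary, statistical analysis, item 2: "Data sets of statistical analysis : intention-to-treat (ITT) population". It sets no condition on dosing or evaluation.
- Section 16.3.1: "The full analysis set is the main efficacy evaluation population of this study". After citing the ITT principle, it says that "all subjects randomized into groups and those with more than one medication record and efficacy evaluation will be included in the full analysis set".

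Other sections bear on who would meet that rule.

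- Section 10.2 asks for the first study dose within an hour of randomisation. By the section 6.2 table, dosing is daily from then on.
- Section 7.5.2 lists, among circumstances for permanent discontinuation at the investigator's decision, "Primary outcomes (ischemic or hemorrhage stroke) occur".
- Section 7.5 says that stopping study drug for any reason is neither withdrawal nor the end of follow-up. Section 7.5.3 asks for 90-day follow-up after permanent discontinuation.
- Section 7.6: "Subjects who were randomized and had one or more doses recorded were required to complete the calendar visits according to the protocol".
- Section 16.3 calls itself an overview and defers the full set of planned analyses to a final SAP before database lock. That SAP is not shown.

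**The concern.** An ITT analysis keeps every randomised patient, so that the groups compared are those formed by randomisation. A condition on medication records is met or failed after randomisation, and here the primary event can decide it. If a stroke on the first treatment day leads to permanent discontinuation, the patient may have only one dosing record. The event would be known, because follow-up continues, but the patient would fail the stated rule.

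Two features make that window relevant. Section 1.1 says that recurrence risk in large-artery disease is high in the first 7 days after onset, and the trial enrols up to 72 hours after onset. The section 6.2 table also has both factors differing from day 1: clopidogrel loading against placebo, and atorvastatin against placebo on days 1-3. If early events differ by arm, removing some of them could shift both marginal hazard ratios. The documents do not fix the direction of any shift.

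**Working it through.** **1. Side-by-side reading.** The Summary includes all randomised patients. Section 16.3.1, on its natural reading, includes randomised patients who also have more than one medication record and an efficacy evaluation. If the second clause were not a restriction, it would have no function. The two places therefore describe different sets.

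**2. Which condition matters.** A recorded stroke is itself an efficacy evaluation, and a patient with no evaluation adds almost no follow-up time to a Cox model. Only the medication-record condition can remove an observed stroke.

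**3. The plan's own power figure.** Inputs from section 16.1, Table 2: n = 2896 per marginal group, rates 0.1157 and 0.0930, two-sided alpha 0.05, stated power 0.807. Two-proportion test with pooled variance under the null:

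- Mean rate = (0.1157 + 0.0930)/2 = 0.10435
- Null term = 1.96 × √(2 × 0.10435 × 0.89565) = 0.847
- Difference term = 0.0227 × √2896 = 1.222
- Alternative SD = √(0.1157 × 0.8843 + 0.0930 × 0.9070) = 0.432
- Power = Φ((1.222 − 0.847)/0.432) = 0.807

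The stated figure reproduces (0.8068 unrounded).

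**4. Expected strokes.** 2896 × 0.0930 = 269 and 2896 × 0.1157 = 335, so about 604 per marginal comparison.

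**5. Share at risk of exclusion (assumption).** The documents give no figure for strokes before a second medication record. The window is about one day of 90. A flat hazard gives 1/90 = 1.1%, or about 7 of 604 strokes. Some front-loading is plausible, so 1-5% is used as the range. The lost strokes, and those patients, are removed from both arms in proportion and power is recomputed:

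| Share of strokes lost | Strokes lost | Power |
|---|---|---|
| none | 0 | 0.807 |
| 1% | 6 | 0.803 |
| 2% | 12 | 0.800 |
| 5% | 30 | 0.789 |

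The relative risk stays at about 0.80 throughout.

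**6. Unequal loss (illustration only).** The planned difference is 335.1 − 269.3 = 65.7 strokes. Suppose 5% of control strokes are dropped and 10% of that difference lies in the dropped window. The control arm loses 16.8 strokes and the treatment arm 16.8 − 6.6 = 10.2. The relative risk moves from 0.804 to 0.812 and power falls to 0.747. For scale, at the planned event counts about 24 more strokes would have to be removed from the control arm than from the treatment arm before z falls below 1.96 (z = 1.93).

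**The case against.** Several objections have force.

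- **The sentence is ambiguous.** It opens with the ITT principle and can be parsed as all randomised subjects plus a further group. The threshold may also be a loose rendering of at least one, which is the wording in section 7.6. Both stand as caveats. Even with a one-dose threshold, a stroke between randomisation and the first dose would still drop out, and the conflict with the Summary would remain.
- **A medication record is undefined.** Day-1 dosing involves three products. If each counts as a record, the first administration already meets the rule. This stands, so the text supports saying that strokes can fall out, not that they will.
- **Stopping after a stroke is at the investigator's decision.** True, and this again limits the claim to a possibility.
- **The final SAP may settle it.** It may, but the protocol did not leave the set open; it defined one.

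A reader might also infer more than the documents support.

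- *That patients without an efficacy evaluation take strokes with them.* Step 2 of the working shows why they do not.
- *That the dose thresholds for the efficacy set, the safety set and the visit rule contradict one another.* They serve different purposes and need not match.
- *That undosed patients go unfollowed.* Section 7.6 obliges dosed patients to complete visits; it does not release the others.
- *That power falls substantially.* A 10% proportional loss gives 0.769, but it needs a tenth of all 90-day strokes to fall within about one day. Under version 4.0, TIAs and strokes with NIHSS of 3 or less enter only 24-72 hours after onset. Nothing in the documents supports such a share.

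**Conclusion.** The point holds as a fault of definition. On its natural reading, section 16.3.1 sets a post-randomisation condition on the main efficacy set. That contradicts the Summary and can exclude an observed early stroke because of the stroke itself.

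The size cannot be derived from the documents and is probably small. Under the assumed 1-5% proportional loss, 6-30 of about 604 strokes go and power is 0.803-0.789 against 0.807. The reason to act is possible bias in the two primary comparisons, not a demonstrated loss of power. The conclusion rests on the restrictive reading and on a medication record meaning a dosing occasion; the text settles neither.

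**What to change.** - **Section 16.3.1:** define the primary efficacy set as all randomised patients in their assigned groups, regardless of doses taken or evaluations recorded, with censoring at last known status up to Day 90.
- **Dosed set:** if one is kept, use it only for a sensitivity analysis, and define what counts as a medication record.
- **Summary:** use the same definition, so that the two places agree. Carry it into the final SAP.
- **Section 7.6:** state that every randomised patient is followed to Day 90, dosed or not.

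The cost is wording, plus follow-up contact for any patients who are randomised but never dosed. The planned sample size does not change.

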### **10.3 Day7 visit**

- Record NIHSS score.
- Finish brain histological examinations: including MRT and CT scan. If the brain MRI isn't done before randomization, it should be finished within 7 days after randomization, with complete sequence information (sequences T1+T2+FLAIR+DWI/ADC+MRA are required, SWI/GRE-T2\* if qualified). If head MRI is finished, head CT would not be necessary. If the vascular assessment was completed prior to randomization, it doesn't need to be repeated.
- Finish vascular assessments: assessments of intracranial arteries (including MRA, CTA, DSA) and assessments of extracranial arteries (including neck vascular ultrasound, CEMRA, CTA on the arch, DSA), at least one item each is necessary. If the assessment was completed prior to randomization, there is no requirement to review.
- Cardiac examinations: including echocardiography (transthoracic or transesophageal) and electrocardiography (12-lead ECG or long-range HOLTER).
- Finish high-resolution intracranial arterial MRI (only in high-resolution MRI subgroups): examination needs to be completed within 24 hours since randomization.
- Finish laboratory tests: blood routine, biochemistry (including liver function, renal function, blood lipids, creatine kinase) and coagulation function. If the test is completed within 24 hours of screening or randomization, there is no requirement to review.

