#### **10.5 Day $90 \pm 7$ visit**

- Finish clinical scores (NIHSS, mRS, EQ-5D).
- Finish intracranial arterial high-resolution MRI (only for high resolution MRI subgroups).
- Finish laboratory tests: blood routine and biochemical panel (including liver function, renal function, blood lipids, creatine kinase). Fasting venous blood sample should be collected at the same time, and serum, plasma and white blood cells should be extracted and stored separately (Instructions are listed in the biological sample collection handbook).
- Record concurrent medication since last visit.
- Evaluate the compliance of the subject since the last visit.
- Record new strokes and new vascular events since the last visit.
- Record adverse events, bleeding events since the last visit.
- Retrieve study drug box of phase 2 (Study drug from day  $22 \pm 2$  to day 90).
- Summarize the whole study.
- The subject and the investigator decide which anti-platelet drug should be used after the study together.
- Inform the subject for long-term follow-up, make an appointment of the next visit: 12th month  $\pm$  14 days after administration.

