#### **10.6 12th month $\pm$ 14 days visit**

- Record clinical scores (mRS, EQ-5D).
- Record personal history of the subject, especially smoking and drinking history.
- Record concurrent medication since last visit.
- Record new strokes and new vascular events since the last visit.
- Record adverse events, bleeding events since the last visit.

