#### 16.3.2.2 Efficacy analysis

- 1) Primary outcome:

Survival curves will be estimated for the primary outcome using the Kaplan-Meier procedure and compared using a Cox regression model Wald test, stratified by the opposite arm of the factorial design. First, marginal effects will be compared between intensive and standard antiplatelet therapy, and also between immediate intensive statin therapy (atorvastatin 80mg/d) and delayed intensive statin therapy (atorvastatin 40mg/d). As these are independent comparisons, they have no effect on the type I error rate. For both treatment comparisons, the primary outcome of stroke will be judged to be statistically significant if the treatment test p-value is  $< 0.05$ . Second, if either intensive antiplatelet or immediate intensive statin treatment (atorvastatin 80mg/d) is statistically significant, the effects between combined intensive antiplatelet and immediate intensive statin treatment (atorvastatin 80mg/d) and combined standard antiplatelet and delayed intensive statin treatment (atorvastatin 40mg/d) will be tested. Cox regression model stratified by the opposite arm of the factorial design, will be used in the curative effect assessment and evaluation between the subgroups.

- 2) Secondary outcomes:

- d. Kaplan-Meier curve will be used to simulate the cumulative risk of 90-day follow-up combined with secondary endpoint events such as vascular events, ischemic stroke, TIA, myocardial infarction, vascular death and all-cause death. Cox proportional risk model will be used to calculate HR and the 95% confidence interval and the Log-rank test would be used to evaluate the efficacy;
- e. For ordinal stroke or TIA, ordinal logistic regression will be used to calculate OR and 95% confidence interval. For the poor functional outcome (mRS score 2-6) and early neurological deficits (increase in NIHSS score at 7days) indexes, logistic regression will be used to calculate OR and 95% confidence interval.
- f. The validity of the extreme value would be examined, and the sensitivity analysis would be carried out.

- 3) Safety analysis

The overall of safety assessment is all used test medications and the safety follow-up case should be

recorded at least once. The safety evaluation data includes adverse reactions observed during the trial and changes in laboratory data before and after treatment.

Safety evaluation will be analyzed using safety data set.

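### LOCF, the one missing-value method named for the full analysis set, would usually insert the randomisation-day score for Day 90 mRS, Day 90 EQ-5D and Day 7 NIHSS

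*Supplement*

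**What the plan says.** Protocol version 4.0, Section 16.3.1, makes the full analysis set (FAS) the main efficacy population and states: "When choosing FAS to analyze, the estimate of the missing value, the last observation carried forward (LOCF) estimation method can be used". No other method for missing values is named. The sensitivity analysis in Section 16.3.2.2 is mentioned together with extreme values, not with missing data.

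The visit schedule (Sections 10.2 to 10.6 and the table in 10.9) fixes when each scale is scored:

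- Day of randomisation, Section 10.2: "EQ-5D score and neurological examination (including mRS and NIHSS".
- Day 7, Section 10.3: "Record NIHSS score". NIHSS is the only one of the three scales at this visit, and likewise at Day 14 or discharge (Section 10.4).
- Day 90, Section 10.5: "Finish clinical scores (NIHSS, mRS, EQ-5D".
- Month 12, Section 10.6: "Record clinical scores (mRS, EQ-5D".

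On analysis, Section 16.3.2.2 states: "For the poor functional outcome (mRS score 2-6) and early neurological deficits (increase in NIHSS score at 7days) indexes, logistic regression will be used". The six-level ordinal stroke/TIA scale, as set out in Section 2.2.1, also uses the 90-day mRS.

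**The concern.** LOCF needs an earlier value that says something about the outcome. For Day 90 mRS and EQ-5D, the only earlier scheduled value is the one taken on the day of randomisation, within 72 hours of onset. For Day 7 NIHSS it is normally the baseline score too. The patient is then analysed as if nothing had changed since randomisation.

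For mRS and EQ-5D the error can go either way: a patient who recovered is scored too badly, and one who had a later stroke is scored too well. For early neurological deficit it goes one way, because baseline minus baseline is zero and so cannot be an increase. On the ordinal scale, a patient with a new stroke but no Day 90 mRS would be graded by an mRS taken before that stroke.

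At stake are the rates of poor function, poor quality of life and early deterioration, and the severity grading of new strokes. Filled-in values would also be treated as observed.

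**Working it through.** **Plan's own figures.** Section 16.1 gives 6100 patients, 5% loss, and 2896 evaluable patients per marginal arm with rates 0.0930 and 0.1157. A two-proportion test with pooled variance, two-sided 0.05, gives power 0.807, as stated. The inflation also reproduces: 1448/0.95 = 1524.2, stated as 1525; 2896/0.95 = 3048.4, stated as 3050 (2 × 1525). The point does not rest on these figures; they only supply the 5%.

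**What LOCF can carry forward.**

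| Missing value | Scheduled values before it | LOCF inserts |
|---|---|---|
| Day 90 mRS | randomisation | randomisation-day mRS |
| Day 90 EQ-5D | randomisation | randomisation-day EQ-5D |
| Day 7 NIHSS | randomisation | baseline NIHSS, change 0, unless an interim score exists |

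Month 12 scores come too late to be carried forward. A Day 14 NIHSS, where present, is ignored for Day 7 because LOCF only looks backward. An NIHSS before Day 7 can arise from an early discharge visit (Section 10.4) or a suspected neurological event (Section 10.7). Neither route adds an mRS or EQ-5D.

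**Size within an arm.** Let m be the fraction missing, q the true event rate among the missing, and b the rate that LOCF codes for them. The arm's rate shifts by m × (b − q). With m = 0.05 as an illustration:

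- patients affected: 0.05 × 6100 = 305 in all, 0.05 × 3050 = 152.5 per marginal arm;
- shift per 10-point gap: 0.05 × 10 = 0.5 points.

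**Day 7 outcome.** Assume no interim score, so b = 0, and true event rates of 5% to 20% (the documents give none).

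- Missingness unrelated to outcome: 5% of events are lost; a true 10% is recorded as 0.95 × 10% = 9.5%.
- Missing patients at k times the risk of the others: the share of events lost is 0.05k/(0.95 + 0.05k). For k = 2 this is 0.10/1.05 = 9.5%; for k = 4 it is 0.20/1.15 = 17.4%.

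**Size between arms.** The bias in the risk difference is m1(b1 − q1) − m0(b0 − q0).

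- No true effect, equal missingness with the same link to outcome: the terms cancel and the null odds ratio stays 1.00.
- True effect, equal 5% missing unrelated to outcome: the Day 7 risk difference shrinks by the factor 0.95.
- No true effect, but 7% against 3% missing (assumed): a 10% rate is recorded as 0.93 × 10% = 9.3% and 0.97 × 10% = 9.7%. The odds ratio is (0.093/0.907)/(0.097/0.903) = 0.955, and with 3050 per arm the nominal 5% test rejects 8.3% of the time. At true rates of 5% and 20% the odds ratios are 0.957 and 0.949, and the rejection rates 6.6% and 12.5%.

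**Precision.** Counting 5% imputed values as observed narrows the standard error by about 1 − √0.95 = 2.5%, which is minor.

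**The case against.** The strongest defence is that Section 16.3 calls itself an overview and leaves the planned analyses to a final SAP, which is not shown. The LOCF wording is permissive and tied to no endpoint. That stands as a limit: the absence of endpoint-by-endpoint rules is no finding. But the protocol does name a method, and its own schedule makes that method unsuitable for these outcomes.

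Several stronger readings are tempting, and the documents do not support them.

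- A reader might infer that LOCF carries a stroke-free status to Day 90 and so contradicts the primary analysis. Nothing in the text applies LOCF to stroke. Section 16.3.2.2 uses Kaplan-Meier and Cox methods, which censor incomplete follow-up.
- A reader might infer that every missing Day 7 NIHSS becomes a non-event. Section 10.7 calls for an NIHSS when neurological symptoms are suspected, including worsening of the index event, and early discharge also yields one. Some deteriorating patients would have a score to carry.
- A reader might infer that very ill or dead patients are coded as well. Appendix 3 gives scoring rules for coma, and the mRS range of 2 to 6 takes in a known death. For EQ-5D after death the text is simply silent.
- A reader might take 305 as the number of patients who would receive a baseline value. The 5% is a sample-size allowance; no missing rate is given for any scale. FAS entry also requires an efficacy evaluation ("those with more than one medication record and efficacy evaluation will be included in the full analysis set"), so some lost patients may fall outside it.
- A reader might infer demonstrated bias in the treatment comparison. The trial is double-blind, and the inflated rejection rates above depend on an imbalance that is assumed.

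**Conclusion.** The point holds for the secondary scale outcomes: poor function, poor quality of life, early neurological deficit and the ordinal stroke/TIA scale. LOCF there would usually mean baseline carried forward, which says nothing about what happened after randomisation. The primary outcome and the other time-to-event outcomes are not affected.

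The size is modest at the planned loss: 0.5 points in an arm's rate for each 10-point gap, if 5% are missing. A spurious effect requires missingness, or its link to outcome, to differ between arms. Because the harm is confined to secondary outcomes and the wording is permissive, this is something that should be fixed rather than a bar to the primary analysis.

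**What to change.** Delete the LOCF sentence from Section 16.3.1 and put in the SAP:

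- **Time-to-event outcomes:** censor at last known status.
- **Known deaths:** code as mRS 6, and state how death is handled for EQ-5D and for early neurological deficit.
- **Other missing mRS, EQ-5D and Day 7 NIHSS:** multiple imputation by arm, using baseline scores, available Day 7, Day 14 and event-triggered NIHSS, and stroke by Day 90.
- **Sensitivity:** a best/worst-case analysis of the missing values for each of these outcomes.

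The cost is SAP wording and modest programming. No new data are needed, since every variable listed is already collected.
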